#### Low Dose: 420 mg Silymarin three times daily

Since dose-exposure proportionality was observed in  $\Sigma$  Total silymarin exposures over the dose range of 280 to 560 mg silymarin in NAFLD subjects, and 140 to 700 mg silymarin in HCV subjects, a dose of 420 mg silymarin will be used as the lower dose in this Phase II trial as it represents a dose predicted from Phase I data that will result in 40% lower exposures which might be associated with clinically significant differences in pharmacodynamic endpoints when compared to those observed at a dose of 700 mg.

## **2.0 Study Objectives and Endpoints**

### **2.1 Primary Objectives:**

1. To assess the safety and adverse event profile of silymarin over a range of doses compared to placebo
2. To assess the efficacy of silymarin as defined by an improvement in NAS by at least 2 points.

### **2.2 Secondary Objectives:**

1. To compare NAS before and after therapy
2. To characterize changes in ALT during silymarin therapy
3. To compare HOMAr before and after silymarin therapy
4. To explore relationships between silymarin therapy and serum biomarkers (oxidative stress, apoptosis, and fibrogenesis)

5. To characterize the population pharmacokinetics and pharmacodynamics of silymarin isomers including, silibinin A and B, isosilibinin A and B, silicristin, and silidianin following administration of silymarin to subjects with NASH.

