## 2.3 Endpoints

**Efficacy:** The primary outcome variable (endpoint) for efficacy is improvement by at least 2 points in histology (NAS).

**Safety:** The primary outcome variable for safety is the occurrence of a dose-limiting toxicity during the 48-50 week treatment period. Adverse events (AE) will be categorized by severity.

**Adherence:** Will be measured using a summary of missed dose information obtained from patient diaries and dose counts and will be analyzed as both an outcome and as an explanatory variable in exploratory analyses of pharmacokinetic exposure and response.

**Biomarkers:** The following relationships will be explored: dose and change in biomarkers, changes in biomarkers and treatment success, changes in biomarkers and toxicity.

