### Secondary

- Improvement by at least 1 point in histology (NAS) after therapy
- ALT or AST  $\leq$  45 IU/L (approximate normal range) or with greater than 50% reduction in ALT or AST to a value less than 65 IU/L (approximately 1.5 times the upper limit of normal) after therapy
- Insulin resistance measured by HOMAr.

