## **4.2 Baseline/Randomization Procedures**

### *Liver biopsy*

Percutaneous liver biopsy will be performed within 28 days of randomization, during the 28-day period following completion of the lead in phase. The liver biopsy will be performed according to each sites' standard procedures; however, an adequate specimen of at least 1.5 cm in length is recommended. The biopsy core will be processed for histological analysis. The pathologist at each clinical site, or at the central pathology site as described below, will score the liver biopsy according to a grading scheme as described by Brunt et. al. and Promrat et.al., and as modified by the Nonalcoholic Steatohepatitis Clinical Research Network (NSCRN) recommendation. In the NSCRN grading scheme, five features were independently associated with the diagnosis of NASH: steatosis, ballooning, lobular inflammation, fibrosis, and absence of lipogranulomas. A NAS score of at least 4 detected by the local or central pathologist, as determined by each investigator, will be required for entry (Appendix 7).

Four slides from each patient's liver biopsy will be sent to a central pathology site at the Beth Israel Deaconess Medical Center, Boston, MA. The central pathology site will stain the slides (hematoxylin/eosin, trichrome) and the study pathologist will evaluate each biopsy at the end of the study without knowing which slides belong to which patients and assign a NAS. Pre- and post-treatment biopsy NAS will be determined for the primary efficacy analysis. Patients who meet all inclusion and no exclusion criteria at the end of the lead-in period and have liver biopsy findings consistent with NASH (NAS  $\geq$  4) will be randomized. A baseline (randomization) visit will take place within 28 days of successful completion of the lead-in period and following the liver biopsy. During this 28-day period, the inclusion and exclusion criteria will be verified. In addition, the following procedures will take place.

- A history and physical examination will be conducted
- Baseline laboratory studies including liver tests, complete blood count, serum electrolytes, BUN and creatinine, fasting glucose and insulin, and serum silymarin will be obtained
- Fasting serum and urine will be collected for storage and biomarker studies (oxidative stress, apoptosis, and fibrosis)
- Urinalysis
- HOMAr, determined by the formula:

$$\frac{\text{Glucose mg/dL} \times 0.05551 \times \text{Insulin mcUI/mL}}{22.5}$$

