### 6.2 Efficacy Analysis

Tabular and graphical descriptive statistical methods will be used to characterize the study group at baseline in terms of demographic and clinical measures. For each arm of the study, the proportion of participants whose NAS is reduced by at least 2 points ( $\pi$ ) will be estimated

along with corresponding 95% confidence intervals. Point and interval estimates of the distributions of NAS, ALT, fibrosis score, HOMAr, and at baseline will also be tabulated.

The primary null hypothesis, that the proportion of participants whose NAS is reduced by at least 2 points ( $H_{01}: \pi_0 = \pi_1 = \pi_2$ ) will be tested against the general alternative hypothesis,  $H_{a1}$  that response differs in at least one treatment arm via a chi-square test for association with  $\alpha = 0.05$ . If  $H_{01}$  is rejected, then pairwise comparisons of the arms will be examined using a sequentially rejective test procedure (Holm, 1979). Computation of these results for the ITT analysis will comprise the main results of this study.

A per protocol analysis will also be performed. Participants will be included in this analysis if they took at least 80% of the medication.

The null hypotheses of no difference among treatment arms will be tested for the secondary outcomes. For dichotomous outcomes (secondary outcomes 2 and 3 above), the methods described for testing the primary hypothesis will be used. Change in HOMAr will be compared among the groups using either parametric or non-parametric analysis of variance, as appropriate. The null hypothesis of no treatment differences among the three groups for continuous outcomes will be tested using analysis of variance. Post-hoc tests to identify pairwise differences should the null hypothesis be rejected will control for multiple comparisons.

To maximize statistical power, there will not be an adjustment for the multiple outcomes since the results will be used to guide the design of a proposed phase III study.

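### Change in NAS is not named as an endpoint for the secondary objective on NAS; a baseline-adjusted analysis of the score would be more efficient than the 1-point responder cut

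*Protocol*

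**What the plan says.** Protocol section 2.2 lists as its first secondary objective "To compare NAS before and after therapy", with no cut. In section 2.3 the primary efficacy endpoint is a fall in NAS of at least 2 points. Under the Secondary subheading the only NAS item is "Improvement by at least 1 point in histology (NAS) after therapy". The other two items are an ALT/AST responder definition and HOMAr.

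Section 6.2 states three rules for secondary outcomes:

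- "For dichotomous outcomes (secondary outcomes 2 and 3 above), the methods described for testing the primary hypothesis will be used", which means a three-arm chi-square test followed by Holm-adjusted pairwise comparisons.
- HOMAr change has a rule of its own: a comparison of the arms by analysis of variance, in parametric or rank form depending on the data.
- For the remaining case the rule reads: "The null hypothesis of no treatment differences among the three groups for continuous outcomes will be tested using analysis of variance".

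NAS as a score appears in section 6.2 only among the distributions to be tabulated.

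The scores themselves will exist. Under the liver biopsy heading in the baseline procedures, "the study pathologist will evaluate each biopsy at the end of the study without knowing which slides belong to which patients and assign a NAS". The same paragraph has the scores from before and after treatment feed the primary analysis.

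**The concern.** The objective asks how NAS differs before and after treatment. The endpoint named for it records only whether the score fell by at least 1 point. A fall of 1 then counts the same as a fall of 4, and no change the same as a rise. The primary already dichotomises the same score, so no named NAS endpoint uses its full range.

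Section 6.2 says the results will guide a phase III design. For that purpose the estimated difference in NAS for each dose against placebo, with its interval, is a direct result, and two responder rates convey it poorly. If the true effect is smaller than the planning rates in section 6.3, the responder comparisons may well miss a dose effect that the same biopsies could show and size.

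**Working it through.** **Inputs from the protocol.** 40 per arm, three arms, alpha 0.05, and planned 2-point response rates of 15% (placebo), 40% (420 mg) and 55% (700 mg), all from section 6.3. Allocation strata are site and diabetes status (section 6.0).

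**Inputs assumed.** The SD of change in NAS and its correlation with baseline are not given. I take the fall in NAS as normal with SD 1.6, rounded to whole points, a baseline-change correlation of -0.4, and every follow-up biopsy obtained. SD 1.0 to 2.0 serves as a range.

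**The protocol's own figures.** For a 3x2 chi-square, lambda = n x sum(p_i - pbar)^2 / [pbar(1 - pbar)] on 2 df. For the safety rates in section 6.1 (5/10/10%), lambda = 0.87 and power is 12%, as stated. For 15/40/55%, lambda = 14.07 and power is 92.9%, not the stated 83%. The 83% is reproduced by 15% against 47.5%, 40 per arm, at two-sided 0.025. That is a separate matter, errs on the cautious side and does not affect this point.

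**Step 1: calibrate.** A rounded fall of at least 2 means a latent fall above 1.5, so the arm mean is 1.5 - 1.6 x z(1 - p). For 15/25/35% the means are -0.158, 0.421 and 0.883.

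**Step 2: 1-point cut.** P(fall of at least 1) = Phi((mean - 0.5)/1.6) = 0.3404, 0.4803, 0.5947, with average 0.4718. The sum of squared deviations is 0.0324. Lambda = 40 x 0.0324 / (0.4718 x 0.5282) = 5.2, power 52%.

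**Step 3: change in score.** Variance after rounding is 1.6^2 + 1/12 = 2.643. The squared deviations of the means sum to 0.545. Lambda = 40 x 0.545 / 2.643 = 8.25; F on 2 and 117 df gives 72%. The cut keeps 5.2/8.25 = 63% of the information.

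**Step 4: baseline adjustment.** The squared correlation after rounding is 0.16 x 2.56/2.643 = 0.155. Lambda = 8.25/(1 - 0.155) = 9.76; F on 2 and 116 df gives 79%.

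**Step 5: all scenarios.** Power for 1-point cut / ANOVA of change / ANCOVA with baseline:

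| True 2-point rates | Formula | Simulation (about) |
|---|---|---|
| 15/25/35% | 52 / 72 / 79% | 56 / 74 / 80% |
| 15/30/40% | 70 / 88 / 93% | 72 / 88 / 92% |
| 25/35/45% | 39 / 56 / 64% | 40 / 58 / 64% |
| 15/40/55% (planned) | 96 / >99 / >99% | 97 / >99 / >99% |

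A repeat of 3,000 simulated trials per scenario agreed with the simulation column to within 4 points. Its rejection rate under no effect was 5 to 6% for these three tests. Site and diabetes status were not modelled.

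**Step 6: range of SD.** With SD 1.0 to 2.0 the formula gives 51-52% for the cut against 70-72% for ANOVA of change at 15/25/35%, and 69-70% against 86-88% at 15/30/40%. Over these and the planned rates the cut keeps 59-65% of the information. Because the means are calibrated to the response rates, the result depends little on the SD.

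**The case against.** The strongest reply is that this concerns a secondary objective on which the trial was not sized, that the 1-point cut does well at the planned effect, and that covariates for a secondary model are often left to a statistical analysis plan, which is not at hand. The first two parts stand and limit the point's weight. The third stands in part: the protocol does choose the endpoint and does name analysis of variance, so there is a stated choice to improve on.

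Three stronger readings are tempting, and the protocol does not support them.

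- *That the objective is answered only by the cut.* Section 6.2 tabulates NAS distributions, and its general sentence on continuous outcomes comes after HOMAr has had a sentence of its own, so it could take in change in NAS. That change is unnamed; it is not excluded.
- *That a 1-point cut is noisier than the 2-point primary and therefore weaker.* It does admit more placebo responders: 34% under this model when 15% pass the 2-point cut. But it has more power in every scenario, for example 54% against 44% at 15/25/35% and 73% against 62% at 15/30/40% in the repeat simulation. The right comparison is with the full score.
- *That the 1-point outcome has no test assigned.* The list in section 2.3 is unnumbered. If the primary counts as outcome 1, outcomes 2 and 3 are the two dichotomous ones. The 1-point outcome is dichotomous, so its test can be worked out. Read by position in the secondary list, however, outcome 3 is HOMAr, so the reference is loose.

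The missing-biopsy objection also has force. Section 6.3 counts a participant without a follow-up biopsy as a treatment failure, which defines a responder status but not a change score.

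**Conclusion.** The point holds as an efficiency and clarity improvement. It does not question the validity of the primary analysis. The objective is about the score, the named secondary endpoint is a cut of it, and change in NAS is neither listed as an endpoint nor given a baseline-adjusted comparison.

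For effects below plan, using the score gains about 16 to 18 points of power over the 1-point cut with ANOVA, and about 20 to 24 points with ANCOVA. At the planned 15/40/55% the gain is about 3 points. These sizes rest on the rounded normal shape and complete biopsies. The step from ANOVA to ANCOVA rests wholly on the assumed correlation of -0.4. The direction of the cut-versus-score comparison was the same in every scenario and at every SD tried.

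**What to change.** Keep the 2-point responder endpoint as primary and the 1-point rate as a supporting secondary. For the first objective in section 2.2, add change in centrally read NAS as a named secondary endpoint. Analyse it by ANCOVA with baseline NAS, site and diabetes status as covariates, and report each dose-minus-placebo difference with a 95% confidence interval. Analyse change in HOMAr with its baseline value as a covariate.

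State how a participant without a follow-up biopsy enters the change-score analysis, because the treatment-failure rule in section 6.3 covers responders only.

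In section 6.2, replace the reference to outcomes 2 and 3 with the names of the outcomes meant, so that it plainly covers the 1-point NAS and ALT/AST responder outcomes and not HOMAr.

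The cost is one additional secondary analysis, one missing-data rule and a wording correction. No new data are needed, and section 6.2 already plans no adjustment across outcomes, so no other test loses alpha.

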## 2.3 Endpoints

**Efficacy:** The primary outcome variable (endpoint) for efficacy is improvement by at least 2 points in histology (NAS).

**Safety:** The primary outcome variable for safety is the occurrence of a dose-limiting toxicity during the 48-50 week treatment period. Adverse events (AE) will be categorized by severity.

**Adherence:** Will be measured using a summary of missed dose information obtained from patient diaries and dose counts and will be analyzed as both an outcome and as an explanatory variable in exploratory analyses of pharmacokinetic exposure and response.

**Biomarkers:** The following relationships will be explored: dose and change in biomarkers, changes in biomarkers and treatment success, changes in biomarkers and toxicity.

### Secondary

- Improvement by at least 1 point in histology (NAS) after therapy
- ALT or AST  $\leq$  45 IU/L (approximate normal range) or with greater than 50% reduction in ALT or AST to a value less than 65 IU/L (approximately 1.5 times the upper limit of normal) after therapy
- Insulin resistance measured by HOMAr.

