### 3.2 Study Population

Participants will be at least 18 years old, have serum AST or ALT > 40 IU/L, and demonstrated fatty liver.

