#### Inclusion Criteria

- Age at least 18 years at the start of the lead-in period
- AST or ALT greater than 40 IU/L within one year of the start of the lead-in phase and at least once during the lead-in phase
- Successfully complete a 28-day lead-in phase. Successful completion of the lead-in phase will require the participant's BMI at the end of the lead-in period to be within +/- 10% of their BMI obtained at the initial lead-in visit, as well as adherence to the alcohol consumption guidelines.
- Have a liver biopsy performed within 18 days of completing the lead in phase demonstrating features consistent with NASH without cirrhosis; NAS score of at least 4.
- Negative urine pregnancy test (for women of childbearing potential) documented within the 24-hour period prior to the first dose of study medication. Females of childbearing

potential must be using two reliable forms of effective contraception during the study (while on study drug and during follow-up)

- Demonstrated fatty liver on an imaging modality, either ultrasound, CT, or MRI, within 1 year of the start of the lead-in phase
- Participant agrees to discontinue use of other antioxidants such as vitamin E, vitamin C, glutathione, alpha-tocopherol, or non-prescribed complementary alternative medications (including dietary supplements, megadose vitamins, herbal preparations, and special teas) from the start of the lead-in phase through completion of the follow-up phase. A multivitamin at standard doses will be allowed.
- Participant agrees to discontinue use of silymarin or other milk thistle preparations, other than study medication, from the start of the lead-in phase through completion of the follow-up phase

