##### **Visit 2 (Day 28)**

Subjects will return for the final lead-in visit to evaluate whether they can proceed to the treatment period. At this visit, a physical examination (including weight and vital signs), BMI and any changes in medical history as compared to the first lead-in visit will be recorded. Blood tests will be done for complete blood count including platelet count, chemistry, liver enzymes, and a routine urinalysis. Blood will be collected for future studies. Patients with at least one liver enzyme greater than 40 IU/L (AST or ALT) will have a liver biopsy performed ideally within 14 days, but allowable up to 18 days, of completion of the lead-in phase. The liver biopsy results must be obtained prior to moving on to the treatment phase.

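### The secondary liver-enzyme responder endpoint has no baseline condition, so some eligible participants already meet it before the first dose

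*Protocol*

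**What the plan says.** The second entry under Secondary in protocol section 2.3 defines the enzyme endpoint in two limbs. A participant responds if ALT or AST after therapy is at or below "45 IU/L (approximate normal range) or with greater than 50% reduction in ALT or AST to a value less than 65 IU/L". The first limb is a level. Only the second limb refers to where the participant started.

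The enzyme condition for entry is also an either-or rule, with a lower cut-off. Section 3.2 reads "Participants will be at least 18 years old, have serum AST or ALT > 40 IU/L, and demonstrated fatty liver". The inclusion criteria ask for "AST or ALT greater than 40 IU/L within one year of the start of the lead-in phase" and for such a value at least once in the lead-in. At the second lead-in visit, "Patients with at least one liver enzyme greater than 40 IU/L (AST or ALT) will have a liver biopsy performed".

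Section 6.2 says that for dichotomous secondary outcomes "the methods described for testing the primary hypothesis will be used". That means comparing the three arms "via a chi-square test for association with" a 0.05 level, followed by Holm pairwise comparisons. It does not limit the enzyme endpoint to participants who were abnormal at baseline.

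**The concern.** A responder endpoint should record a change from a state that did not already satisfy it. Here two features let the starting state satisfy it:

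- **Either-or at both ends.** One enzyme above 40 IU/L admits a participant, and the other enzyme, at or below 45 IU/L, makes the same participant a responder.
- **Overlapping cut-offs.** The response cut-off (45) lies above the entry cut-off (40). A participant whose only raised enzyme is 41-45 IU/L is eligible and already at the response level.

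Timing adds to this. The section on repeating the lead-in allows randomization up to 28 days after the lead-in ends, and up to 42 days if laboratory tests are repeated. Neither that section nor the baseline procedures set an enzyme threshold at randomization. A value above 40 at the last lead-in visit may have drifted down by the first dose.

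Such participants are counted as treatment responses in every arm. The reported rates then mix baseline normality with response, and the difference between arms shrinks. Section 6.2 says the results are meant to guide a phase III design, so an inflated placebo rate and a diluted difference would carry over into that planning.

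**Working it through.** The protocol states no rate, power or sample size for this endpoint, so there is no figure to reproduce. The logical check comes first and needs no assumption. The size that follows does.

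**1. Apply the rule with no change on treatment.** Inputs are the section 2.3 definition and the entry rule (either enzyme above 40).

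| ALT/AST at randomization (IU/L) | Eligible | Endpoint met, no change | Met if both had to be ≤ 45 |
|---|---|---|---|
| 90/42 | yes | yes | no |
| 38/70 | yes | yes | no |
| 44/38 | yes | yes | yes |
| 44/44 | yes | yes | yes |
| 60/50 | yes | no | no |
| 46/46 | yes | no | no |

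Every eligible participant with at least one enzyme at or below 45 IU/L is already a responder. The last column shows that replacing *or* by *and* removes 90/42 and 38/70 but leaves 44/38 and 44/44.

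**2. Share affected (assumed).** The protocol gives no enzyme distribution. I assumed bivariate lognormal values with median ALT 60-80, median AST 45-55, log-SD 0.45-0.5 and correlation 0.7-0.8. I simulated 400,000 participants per scenario and kept those with either enzyme above 40. Across scenarios:

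- at least one enzyme ≤ 45 at baseline: about 29% to 47% of entrants;
- both enzymes ≤ 45 at baseline: about 4% to 9%.

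**3. Dilution, two arms.** Let b be the share who qualify at baseline and stay qualified in every arm, and p the response rate in the rest. The observed rate is p' = b + (1 − b)p, so the absolute difference shrinks by the factor (1 − b). Take an assumed contrast of 20% versus 50% and the 40 per arm of section 6.3. At b = 0.4:

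- 0.4 + 0.6 × 0.20 = 0.52
- 0.4 + 0.6 × 0.50 = 0.70

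The 30-point difference becomes 18 points. Exact power of the uncorrected chi-square test at two-sided 0.05:

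| b | Observed rates | Power |
|---|---|---|
| 0 | 20% vs 50% | 82% |
| 0.04 | 23% vs 52% | 77% |
| 0.09 | 27% vs 55% | 72% |
| 0.20 | 36% vs 60% | 60% |
| 0.40 | 52% vs 70% | 39% |

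**4. The planned three-arm test.** The noncentrality is λ = n Σ(p'ᵢ − p̄)² / [p̄(1 − p̄)] with n = 40, where p̄ is the mean of the three observed rates. Power is the chance that a noncentral chi-square on 2 df exceeds 5.99. I borrowed 15%, 40% and 55% from the NAS assumptions in section 6.3 as rates among participants not already qualifying:

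| b | Observed rates | λ | Power |
|---|---|---|---|
| 0 | 15/40/55% | 14.07 | 92.9% |
| 0.20 | 32/52/64% | 8.36 | 73.8% |
| 0.40 | 49/64/73% | 4.99 | 50.3% |

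The 92.9% is only the starting point of this illustration. It is not a check of the 83% that section 6.3 gives for the NAS endpoint. Both tests show the same pattern: the loss is modest when b is below one tenth and large when b approaches 0.4.

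**The case against.** **The wording may mean whichever enzyme was raised.** The secondary list is loosely written: section 6.2 calls secondary outcomes 2 and 3 dichotomous, yet the third entry is HOMAr. But the protocol does not state this reading, and it does not close the gap. If every enzyme above 40 had to reach 45 or less, participants with both enzymes at or below 45 would still qualify at entry (4-9% in the illustration, power 72-77% instead of 82%). If one raised enzyme were enough, 90/42 would still qualify too. What stands is that the larger power loss belongs to the literal reading.

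**The evaluable set could be left to a SAP.** Details can be. This, however, is a stated definition that returns a wrong classification, and a SAP could repair it only by departing from the protocol text.

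**A reader might infer that the comparison is biased toward silymarin.** The documents do not support that. Randomization spreads baseline qualifiers over the arms, so the expected effect is higher rates everywhere and a smaller contrast.

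**A reader might infer that the endpoint must be ALT alone**, because objective 2 in section 2.2 is "To characterize changes in ALT during silymarin therapy". That is not decisive. The protocol Summary speaks of liver enzymes in its specific objectives and names change in liver enzymes as a secondary endpoint, so a two-enzyme endpoint is consistent with it. ALT alone would also leave the 41-45 overlap.

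**A reader might call the enzyme result uninterpretable.** That goes too far. Enzymes are measured at baseline and at each visit, so the share qualifying at baseline can be reported. The Summary's change in liver enzymes, together with the analysis of variance that section 6.2 plans for continuous outcomes, at least contemplates a continuous enzyme analysis.

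**Conclusion.** The point holds as a defect of definition. As written, an eligible participant with one enzyme at or below 45 IU/L at randomization meets the secondary enzyme endpoint without any change. This follows from sections 2.3, 3.2, 3.3 and 6.2 alone.

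The consequence is inflated response rates in all arms and a diluted treatment contrast. It is not a systematic bias, and the primary NAS analysis is unaffected. The endpoint is secondary in a phase II trial, so this should be fixed, but it does not threaten the main result.

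The size is uncertain. The 29-47% and 4-9% shares rest on assumed enzyme distributions. The power figures also rest on an assumed contrast and on every baseline qualifier remaining one. The fall from 82% to 39% should be read as what a 40% share would do, not as an estimate for this trial. The protocol claims no power for this endpoint, so no stated figure is wrong.

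**What to change.** Add a baseline condition to the second entry under Secondary in section 2.3, and carry it into section 6.2. Either form works:

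- judge response only on an enzyme that was above 45 IU/L at randomization, stating whether one such enzyme is enough or all must respond; or
- require the criterion for both enzymes.

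In both cases, evaluate the endpoint only in participants who do not already meet the revised criterion at randomization. Changing *or* to *and* without this restriction is not enough, because of the 41-45 overlap. The amendment should be made before unmasking.

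The cost is protocol wording and a smaller denominator. Under the assumptions above, either form would drop the 4-9% with both enzymes at or below 45, which is about 2 to 4 of 40 per arm (0.04 × 40 = 1.6; 0.09 × 40 = 3.6). Keeping the current either-enzyme rule and simply excluding those who meet it at baseline would drop 29-47%, about 12 to 19 of 40 (0.29 × 40 = 11.6; 0.47 × 40 = 18.8). That is a reason to revise the rule as well as the evaluable set.

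No new data are needed, since liver tests are already scheduled at the baseline visit. A baseline-adjusted analysis of log-ALT in all participants can be reported alongside. It keeps everyone, but it is a supplement and does not replace the corrected definition.
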